### RDTs have recently been introduced into government health facilities in Uganda. Government health staff in the study area will therefore receive additional supportive training to use RDTs and to only provide treatment with Coartem® after a positive result. The study will ensure that public health facilities are well stocked with RDTs, antimalarials and other essential drugs through the government credit supply system. Community sensitization meetings will be carried out to increase awareness of ACTs, reasons for the new treatment policy for malaria, the need for better diagnosis, and importance of adherence to treatment.

| **Private facilities (pharmacies and drug shops)** |
| --- |
| Drug shops randomised to either:  1) Confirmatory diagnosis with RDTs, followed by sale of a commercially-available ACTs only to those who have a positive RDTs  **or**  2) Current practice:  Presumptive clinical diagnosis and treatment of fever |

*Key strengths to the study site*

- - Multiple sampling points within the same district and health system
  - Study design allows comparison between private and public health care providers to assess patient preferences

This allows direct comparison of the effectiveness of treatment, and the cost-effectiveness of improved diagnosis, in a range of different health care providers within the same country.

*Primary endpoints*

- Proportion of patients receiving appropriate treatment from a commercial drug outlet: % of patients diagnosed with malaria who receive appropriate[[1]](#footnote-2) ACT treatment (irrespective of time since onset of treatment).
- Over-prescription: % of patients, who are not parasite-positive, who receive inappropriate ACT treatment from a commercial drug outlet.
- Provider adherence to RDT result: % of patients who receive appropriate treatment, consistent with RDT result
- Cost-effectiveness of RDT compared to presumptive treatment in home management of uncomplicated malaria.

All endpoints will be examined and reported according to age and sex: children aged 0-4y, 5-15y and adults ≥ 16y. For each age group, the proportion of patients receiving appropriate treatment will be compared between shops with RDTs and shops without RDTs, in order to determine whether diagnostic testing reduces overuse of antimalarials in that age group.

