***Evaluation***

*Appropriateness of treatment and/or referral*

Prescription patterns and drug sales in private shops and clinics will be measured through the use of exit interviews, drug sales records and mystery shopper visits. Drug sales records will be adapted to include data on RDT results. Semi-structured exit interviews will be used to ascertain whether diagnostic testing was offered, was accepted by the patient, and type and quantity of drugs sold. Exit interviews will also investigate the patient’s perception of diagnostic testing and their knowledge and understanding of the test result, treatment advice and/or referral. In non-intervention areas, a finger-prick blood sample will be taken to prepare a research blood film to ascertain by microscopy whether the fever was due to malaria. A random sample of patients will also be followed at home after several days to ascertain adherence to treatment (see section below), outcome of the illness and total household expenditure on treatment. Patients will be recruited on exit from the drug outlet and individual informed consent will be sought from patients (parents or guardians, in the case of minors) to participate in an exit interview and any subsequent household visits.

The appropriateness of treatment provided will be evaluated as the proportion of correctly treated malaria cases, based on the “gold standard” of the research blood slide read by an experienced research technician. Appropriate treatment of fever is a composite definition including both a) those who a slide-positive who are given a 1st-line antimalarial and b) those who are slide-negative who are not given a 1st-line antimalarial. Over-prescription will also be assessed as the proportion of children who are not parasite positive who receive inappropriate ACT treatment.

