### *Sample size requirements*

### Sample size requirements for a cluster-randomised trial15 were calculated for the primary endpoint of the proportion of patients receiving appropriate treatment (in line with parasitological status). Appropriate treatment is defined as a composite including both a) those who are slide-positive who purchase an ACT and b) those who are slide-negative who do not purchase an ACT or other antimalarial drug. As the priority for improving treatment in the private sector is to increase the proportion of true cases that purchase and use an ACT (as opposed to antipyretics only, without any antimalarial treatment), we do not include prompt appropriate treatment within 24 hours as the primary endpoint in this work package.

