### Studies indicate that less than 40% of adults and less than 25% of children visiting a drug shop will purchase an antimalarial.3,4 Conservatively assuming a baseline level of ACT purchase in 50% of consultations, sample size was calculated to demonstrate an increase in appropriate purchase of an ACT among RDT-positive patients to 75%, and a decrease in inappropriate treatment among RDT-negative patients to 20%. A cluster-randomised trial with 90% power at the 95% significance level and variation between clusters k=0.25, will require a total of 10 clusters per arm, with 61 consultations per cluster (a total of 610 consultations in each arm). A minimum of 620 patients within each age group will thus be recruited at participating outlets in each arm, yielding an overall total of 1240 patients aged 0-4y; 1240 aged 5-14y; and 1240 adults (a total of approximately 375 patients per outlet). Sample size calculations, repeated for lower levels of antimalarial purchase at baseline, required <10 clusters per arm.

The unit of randomization is the community, defined as the census enumeration area. The study will thus be conducted in 20 enumeration areas in two neighbouring sub-counties within Mukono District. Registered drug outlets located in the 10 enumeration areas randomized to the intervention will be trained in the use of RDTs, and drug outlets located in the other 10 enumeration areas will continue their current practice (presumptive diagnosis and treatment).

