**To signify agreement to this**

**Type initials of corresponding PI with date:** [name]

**Type initials of lead PI(s)* with date:** [name]; [name]

1. The proportion of correctly treated malaria cases is based on the “gold standard” of a blood slide read by an experienced research technician. Appropriate treatment is a composite definition including both a) those who a slide-positive who are given a 1st-line antimalarial and b) those who are slide-negative who are not given a 1st-line antimalarial (irrespective of dosing). [↑](#footnote-ref-2)

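### The protocol ties its conclusion on antimalarial overuse to the composite of appropriate treatment, which also rises when more slide-positive patients obtain ACT, rather than to its own over-prescription endpoint

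*Protocol*

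**What the plan says.** Protocol section (c), Primary endpoints, closes with a comparison by age group. It says that the share of patients who are treated appropriately "will be compared between shops with RDTs and shops without RDTs, in order to determine whether diagnostic testing reduces overuse of antimalarials".

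Three places define the measure as a composite:
- Footnote 1, attached to the first primary endpoint: "Appropriate treatment is a composite definition including both a) those who a slide-positive who are given a 1st-line antimalarial and b) those who are slide-negative" and not given the first-line drug.
- Evaluation, on appropriateness of treatment: "Appropriate treatment of fever is a composite definition including both a) those who a slide-positive who are given a 1st-line antimalarial", together with slide-negatives who are not given one.
- Sample size requirements: "Appropriate treatment is defined as a composite including both a) those who are slide-positive who purchase an ACT and b) those who are slide-negative" and buy neither an ACT nor another antimalarial.

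The slide-positive part is expected to move. The sample size section says that "the priority for improving treatment in the private sector is to increase the proportion of true cases that purchase and use an ACT", and it plans for "an increase in appropriate purchase of an ACT among RDT-positive patients to 75%, and a decrease in inappropriate treatment among RDT-negative patients to 20"%, from a 50% baseline.

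The same list of primary endpoints has a direct measure of overuse: "Over-prescription: % of patients, who are not parasite-positive, who receive inappropriate ACT treatment from a commercial drug outlet". The protocol adds: "All endpoints will be examined and reported according to age and sex". The sentence about overuse does not refer to that endpoint.

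**The concern.** Overuse means giving the drug to patients without parasites. Only the slide-negative half of the composite carries that information. The comparison asks whether a prevalence-weighted sum of two components differs between arms, while the stated purpose is to learn whether one of them has improved.

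The two questions would coincide if the slide-positive component were expected to stay still, but the protocol plans a 25-point rise in it. A significant composite could therefore reflect better treatment of true cases alone, and the protocol's sentence would support reporting it as reduced overuse. Less over-prescription is the first hypothesis under Aim and objectives, so it matters which endpoint carries that conclusion.

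**Working it through.** **Inputs from the protocol (Sample size requirements).** 10 clusters per arm; m = 61 consultations per cluster; k = 0.25; 90% power; 5% significance, read as two-sided; baseline ACT purchase 50%; targets 75% in test-positives and 20% in test-negatives.

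**Assumptions.** Slide prevalence π among shop clients is not given; 30%, 50% and 70% are used. The targets for RDT-positives and RDT-negatives are read as slide-positive and slide-negative rates. The 50% baseline applies to both groups. k applies to the composite.

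**1. Reproduce the stated size.** With

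v = p0(1−p0)/m + p1(1−p1)/m + k²(p0² + p1²),

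clusters per arm = (1.960 + 1.282)² × v / (p1 − p0)², with 1 added in the small-sample form.

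For 50% v 75%: v = 0.00410 + 0.00307 + 0.05078 = 0.05795, and 10.507 × 0.05795 / 0.0625 = 9.74. This rounds to the stated 10 without the added 1; with it the result is 10.74. The power checks below keep the added 1, which lowers the figures slightly.

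**2. Composite.** C = π × P(ACT | slide-positive) + (1−π) × [1 − P(ACT | slide-negative)]. At baseline C = 50% whatever π is.

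**3. Slide-positives rise from 50% to 75%; chance of a significant composite.** Power = Φ(√[(10−1)(p1−p0)²/v] − 1.960). Worked case, π = 50%, overuse unchanged:
- C = 0.5 × 0.75 + 0.5 × 0.50 = 62.5%
- v = 0.00410 + 0.00384 + 0.04004 = 0.04798
- √(9 × 0.015625 / 0.04798) = 1.712
- Φ(1.712 − 1.960) = 40%

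| π | C, overuse stays 50% | Formula | Simulation | C, overuse rises to 60% | Formula | Simulation |
|---|---|---|---|---|---|---|
| 30% | 57.5% | 19% | 19% | 50.5% | 3% | 3% |
| 50% | 62.5% | 40% | 40% | 57.5% | 19% | 19% |
| 70% | 67.5% | 64% | 63% | 64.5% | 50% | 51% |

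The simulation used 20,000 trials per cell, beta-distributed cluster means with CV 0.25, binomial counts of 61 and a t-test on 10 v 10 cluster proportions, counting significance in the favourable direction. Placing k on each component's sale rate instead gives about 28%, 60% and 78% for unchanged overuse, and 3%, 27% and 62% for worse overuse.

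**4. How much extra overuse the composite can absorb.** C stays above baseline until overuse has risen by 0.25 × π/(1−π): to about 61% at π = 30% and to 75% at π = 50%. At π = 70% the limit exceeds 100%.

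**5. The direct comparison.** Slide-negatives per cluster: 61 × 0.7 ≈ 43 at π = 30%, and 61 × 0.3 ≈ 18 at π = 70%. With no change in overuse, the slide-negative comparison is significant in the favourable direction in about 2.5% of simulated trials. For 50% v 20% its simulated power is about 99% or more across the range. By formula, 50% v 20% needs 3.90 clusters per arm with 61 slide-negatives each, or 5.51 with 20 each, against the 10 planned.

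**The case against.** **The direct endpoint is already there.** Over-prescription is a primary endpoint, and the sentence just before the quoted one has every endpoint reported by age and sex. Unchanged or worse overuse would appear beside the composite. This stands and limits the harm. It does not correct the sentence, which is the only one in that section saying how reduced overuse is to be determined, and which names the other measure.

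**No formal decision rule is stated.** The protocol gives a comparison and a purpose, with no test or threshold, and an SAP may supply these. That is fair; the test used above is an assumption. But the pairing of this conclusion with this measure is explicit protocol text, so it is not a detail left open.

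**Readings that go too far.**
- A reader might infer that the trial will declare reduced overuse wrongly. That would require setting aside a co-listed primary endpoint, and at 30% prevalence with overuse 10 points worse the chance is only about 3%.
- A reader might infer that a real fall in overuse is likely to be missed because the site is high transmission. The protocol gives no prevalence among shop clients, and transmission level does not fix it for each age group. That scenario also holds slide-positives still. With both components moving as planned, simulated composite power is about 87% to 90%.
- A reader might take the first endpoint bullet, with its denominator of patients diagnosed with malaria, to exclude slide-negatives altogether. Footnote 1 is attached to that bullet and brings them in.

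**Conclusion.** The point holds as a mismatch between a stated conclusion and the measure assigned to it. The composite does not by itself show reduced overuse, because the gain planned in slide-positives raises it too. With that gain and unchanged overuse it is significant in about 19%, 40% and 63% of trials at 30%, 50% and 70% prevalence; with overuse 10 points worse, in about 3%, 19% and 50%.

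These figures rest on an assumed prevalence, the 50% baseline in both slide groups, a cluster-level analysis at two-sided 5%, and k placed on the composite. Since prevalence is unstated, the size could be small or large. The trial will hold the direct evidence on overuse, so this is a correction worth making to the wording of the conclusion and not a failure of the design.

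**What to change.** Reword the last sentence under Primary endpoints so that, in each age group, the conclusion on overuse rests on the over-prescription endpoint: the proportion of slide-negative patients who receive the drug, compared between arms. Keep the composite as the overall measure of appropriate treatment, always shown with its slide-positive and slide-negative components, and draw no conclusion on overuse from it alone.

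In the same edit, state whether over-prescription means ACT only or any antimalarial. The endpoint bullet and the Evaluation section count ACT; the sample size definition counts ACT or any other antimalarial, and the quoted sentence speaks of antimalarials in general. Choosing the wider meaning would change a primary endpoint and should be declared as such.

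The cost is a few lines of text. No data are needed beyond the slide and sales records that the composite already requires. Each comparison then uses only slide-negatives, about 18 to 43 per cluster, with power of about 99% or more for the planned 50% to 20%.

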### *Secondary endpoints*

- Proportion of patients receiving prompt effective treatment from a commercial drug outlet: % of patients diagnosed with malaria who receive appropriate2 ACT treatment within 24 hours of onset of malaria.
- Acceptability of RDTs: % of patients offered a diagnostic test, % of ACT sales preceded by a test
- Perceptions of ACTs and other antimalarial drugs (amongst community; drug sellers; health staff)
- Perceptions and acceptability of malaria diagnosis using RDTs (amongst community; drug sellers; health staff)
- Willingness to offer and perform RDTs to malaria patients (among drug sellers, health workers)
- Patient adherence to prescription (complete dose taken by day 4)
- Referral: Appropriate treatment of RDT negative patients (lack of antimalarial sale and provision of referral); Timeliness and uptake of referral at a health unit by referred patients.
- Coverage of prompt effective treatment: % of patients with fever who received ACT treatment within 24 hours of onset of malaria, measured through household surveys. For comparison with the WHO/RBM indicator in national and international statistics, coverage in children <5 years will be reported separately from older children and adults.
- Source of treatment: % of patients attending health facility for treatment; % visiting a drug shop
- Equity of diagnosis: % of malaria patients receiving a diagnostic test for malaria, across socio-economic groups.
- Equity of treatment: % of patients, who are diagnosed with malaria, receiving treatment with an ACT, across socio-economic groups.

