**Secondary objectives**

1. To assess perceptions and acceptability of the use of RDTs among malaria patients and drug providers.
2. To assess the impact of improved malaria diagnosis on ACT adherence among providers and consumers.

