Patients are free to choose which shops they use, and will be able to choose between outlets that offer diagnostic testing and those that do not, as this service will be openly advertised. Patients seeking treatment for uncomplicated malaria (or fever) from a registered drug shop in the intervention areas will be offered a RDT prior to drug purchase. Verbal consent will be sought from patients accepting the test, to also prepare a blood film from the fingerprick blood sample for the purposes of the research. Patients who decline an RDT test (and patients seeking treatment at registered drug shops in non-intervention areas) will receive presumptive treatment, as per current practice. This outcome (no test) will be recorded and whether an antimalarial was purchased or not.

Community sensitization on the need for treatment of febrile illness within 24 hrs after onset of illness will also be carried out. Sensitization meetings will also aim to increase awareness of ACTs within the community, the need for better diagnosis, and the importance of adherence to treatment.

*Referral mechanism of severe malaria and non-malarial fevers*

Severe malaria: Children with danger signs consistent with suspected severe malaria (WHO definition 2000) will be given pre-referral treatment using a rectal artesunate suppository and referred immediately to the nearest health unit for further treatment. Patients will be referred using an emergency referral form, including details of symptoms and the use of pre-referral treatment. Shops will keep a dated register for referrals and copy of the referral form with personal identifiers (also at health units).

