Patients are free to choose which source of treatment they use, including government health facilities which perform RDT testing, registered drug shops that offer RDT testing and others which use presumptive treatment. Furthermore, it is the patient’s choice which shops they use, and they will be able to choose between outlets that offer diagnostic testing and those that do not, as this service will be openly advertised. Patients seeking treatment for fever from a registered drug shop in the intervention areas will be offered a RDT prior to drug purchase, and have the right to decline the test.

Patients will be recruited on exit from the drug outlet. Individual informed consent will be sought from patients (parents or guardians, in the case of minors) to participate in an exit interview and subsequent follow-up visits at home in order to evaluate the impact of the intervention on malaria treatment. Patients will be informed that participation in the study is completely voluntary and that they may withdraw from the study at any time. Informed consent will also be sought from all informants prior to undertaking any other interviews (focus group discussions, household surveys, etc.).

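### The two percentages listed as acceptability of RDTs do not isolate patient acceptance, and the one based on ACT sales falls as sellers withhold ACT after a negative test

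*Protocol*

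**What the plan says.** The Protocol's Secondary objectives include this one: "To assess perceptions and acceptability of the use of RDTs among malaria patients and drug providers". Under Secondary endpoints the matching quantitative entry is "Acceptability of RDTs: % of patients offered a diagnostic test, % of ACT sales preceded by a test".

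The same list has a separate provider entry, "Willingness to offer and perform RDTs to malaria patients (among drug sellers, health workers". It also has an entry on perceptions and acceptability of RDT diagnosis among community, sellers and health staff, with no percentage attached, and an equity entry on the share of malaria patients who receive a test, by socio-economic group.

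Four procedures bear on how the two percentages behave:
- **Offer.** Under Methods, patients with uncomplicated malaria or fever seeking treatment "from a registered drug shop in the intervention areas will be offered a RDT prior to drug purchase".
- **Refusal.** The ethics section says that patients "will be offered a RDT prior to drug purchase, and have the right to decline the test". Methods adds: "Patients who decline an RDT test (and patients seeking treatment at registered drug shops in non-intervention areas) will receive presumptive treatment".
- **After a test.** Study design has intervention sellers trained to recommend Coartem only after a positive result.
- **Data.** Exit interviews are "used to ascertain whether diagnostic testing was offered, was accepted by the patient, and type and quantity of drugs sold". For patients who decline, Methods says: "This outcome (no test) will be recorded and whether an antimalarial was purchased or not".

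**The concern.** An offer is an act of the seller. A shop that offers the test to everyone and is always refused scores 100% on the first percentage.

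The second percentage has ACT sales as its denominator. A patient who accepts the test, is negative and is not sold ACT leaves both numerator and denominator. A patient who declines and buys ACT presumptively stays in the denominator. The measure therefore responds to positivity and to what sellers do after a negative result, even when the share of patients accepting is constant. Success against over-prescription, which is a primary endpoint, would appear as lower acceptability.

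The practical risk lies in subgroup reporting. The paragraph that closes the Primary endpoints section says that all endpoints will be reported by age and sex. If positivity differs between children and adults, the measure will differ between them even when they accept the test equally often.

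**Working it through.** The Protocol gives no figure for these endpoints, so there is none to reproduce. The check is algebra followed by an illustration.

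**Inputs**
- a = share of patients tested. With every patient offered, this is the acceptance rate. Not stated; assumed 80%.
- p = RDT positivity. Not stated; the site is described only as high transmission. Shown at 20%, 40% and 60%.
- q = share of RDT-positive patients who buy ACT: 75% (Sample size requirements).
- r = share of RDT-negative patients who buy ACT: 20%, the planning value for inappropriate treatment in the same section; 0% represents full compliance.
- s = share of decliners who buy ACT. Not stated; assumed 50%, equal to the baseline purchase level in the sample size section.

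**Formula**

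Share of ACT sales preceded by a test = a[pq + (1−p)r] / {a[pq + (1−p)r] + (1−a)s}.

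Its derivative in r has the sign of a(1−a)(1−p)s. So the share falls as r falls whenever 0 < a < 1, p < 1 and s > 0. It also falls as p falls whenever q > r. It rises with a, and equals 100% when a = 100%. Only the size, not the direction, depends on the assumed values.

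**Per 100 patients, all offered the test**

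Untested ACT sales are 20 × 0.50 = 10 throughout. Tested ACT sales are 80 × [0.75p + r(1−p)].

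| Positivity | r = 20% | r = 0% |
|---|---|---|
| 20% | 24.8/34.8 = 71% | 12/22 = 55% |
| 40% | 33.6/43.6 = 77% | 24/34 = 71% |
| 60% | 42.4/52.4 = 81% | 36/46 = 78% |

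True acceptance is 80% in all six cells. Reading down the r = 20% column, positivity alone moves the measure by 10 points (71% to 81%). Reading across, better compliance lowers it by 16, 6 and 3 points.

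**Sensitivity (r = 20% to r = 0%)**
- Higher positivity (a = 80%, s = 50%, p = 70%): 82.4% to 80.8%.
- Higher acceptance (a = 95%, s = 50%, p = 20%): 92.2% to 85.1%.
- More decliners buying (a = 80%, s = 100%, p = 20%): 55.4% to 37.5%.

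**Offer rate**

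If only a share of patients is offered the test, the share tested is the offer rate times the acceptance rate. An offer rate of 100% with 80% acceptance and an offer rate of 80% with 100% acceptance both give 80% tested. If patients not offered the test buy ACT at the same rate as decliners, the ACT-sales share is identical in the two cases.

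**Proposed measure**

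Accepted divided by offered equals 80% in every cell of the table.

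**The case against.** The strongest reply is that patient acceptability does not rest on this one entry. A separate endpoint covers perceptions and acceptability, and the Evaluation section explores these through focus groups, in-depth interviews and exit interviews, including willingness to pay. Acceptance and refusal are both recorded, so an analysis plan could form the ratio. This stands in part: a reader might infer that the trial does not assess patient acceptability at all, and the document does not support that. But the Protocol itself fixes the two percentages under the label of acceptability, so an analysis plan that followed them would carry the problem forward. This is a stated definition, not a detail left for later.

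Further points on that side also have force:
- The objective covers providers as well as patients, so the percentage offered is a fair provider measure. It overlaps with the willingness entry, but it is not wrong.
- The ACT-sales share does rise with acceptance. A reader might infer that it is unrelated to acceptance. It is not; it is confounded.
- The equity entry counts patients tested. It mixes offer with acceptance, is restricted to malaria patients and is framed by socio-economic group, so it does not fill the gap.
- RDTs are supplied to shops only in the intervention arm, so no between-arm comparison depends on this measure. Seller compliance is reported under its own endpoints, which helps a reader interpret a fall.
- Acceptance, positivity and purchase by decliners are all assumed. At a high-transmission site the milder rows of the table may be nearer the truth.

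**Conclusion.** The point holds as a fault in the definition of a secondary endpoint. Neither listed percentage isolates patient acceptance. The one based on ACT sales moves against the trial's own aim whenever some untested patients buy ACT, and presumptive treatment of decliners makes such sales expected.

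The size depends on inputs that the Protocol does not give. With 80% acceptance and 50% purchase among decliners assumed, going from the planned 20% to 0% sales among negatives costs 16 points at 20% positivity but only 3 at 60%. At 60% the measure (81% or 78%) is close to the true 80%. With complete acceptance there is no distortion. A reader might take the 55% figure as the expected result; it combines low positivity with full compliance, and nothing in the Protocol makes that the likely case.

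The consequence is greatest for results by age and sex, on the reading that all endpoints there includes the secondary ones. The randomised comparison of the primary endpoints is unaffected.

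**What to change.** For intervention shops, define patient acceptability as the percentage of patients offered an RDT who accept it. Take it from the exit interview and cross-check it against the shop's no-test record. Report it next to the percentage of patients offered a test, labelled as a provider measure. Keep the percentage of ACT sales preceded by a test, but as a targeting or process indicator and not under acceptability.

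The cost is a change of wording and one more reported percentage; no new data are needed. The new measure has a weakness of its own: if sellers offer the test mainly to patients likely to agree, accepted over offered is inflated. It must therefore always be read together with the percentage offered.
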